# Effects of high frequency rTMS of contralesional dorsal premotor cortex in severe subcortical chronic stroke: protocol of a randomized controlled trial with multimodal neuroimaging assessments

**DOI:** 10.1186/s12883-022-02629-x

**Published:** 2022-04-01

**Keywords:** Stroke, Hemiplegia, Transcranial magnetic stimulation, Dorsal premotor cortex, Functional MRI

## Abstract

**Background:**

Previous studies have revealed that low frequency repeated transcranial magnetic stimulation (rTMS) on the contralesional primary motor cortex (cM1) is less effective in severe stroke patients with poor neural structural reserve than in patients with highly reserved descending motor pathway. This may be attributed to the fact that secondary motor cortex, especially contralesional dorsal premotor cortex (cPMd), might play an important compensatory role in the motor function recovery of severely affected upper extremity. The main purpose of this study is to compare the effectiveness of low frequency rTMS on cM1 and high frequency rTMS on cPMd in subcortical chronic stroke patients with severe hemiplegia. By longitudinal analysis of multimodal neuroimaging data, we hope to elucidate the possible mechanism of brain reorganization following different treatment regimens of rTMS therapy, and to determine the cut-off of stimulation strategy selection based on the degree of neural structural reserve.

**Methods/design:**

The study will be a single-blinded randomized controlled trial involving a total of 60 subcortical chronic stroke patients with severe upper limb motor impairments. All patients will receive 3 weeks of conventional rehabilitation treatment, while they will be divided into three groups and receive different rTMS treatments: cM1 low frequency rTMS (*n* = 20), cPMd high frequency rTMS (*n* = 20), and sham stimulation group (*n* = 20). Clinical functional assessment, multimodal functional MRI (fMRI) scanning, and electrophysiological measurement will be performed before intervention, 3 weeks after intervention, and 4 weeks after the treatment, respectively.

**Discussion:**

This will be the first study to compare the effects of low-frequency rTMS of cM1 and high-frequency rTMS of cPMd. The outcome of this study will provide a theoretical basis for clarifying the bimodal balance-recovery model of stroke, and provide a strategy for individualized rTMS treatment for stroke in future studies and clinical practice.

**Trial registration:**

Chinese Clinical Trial Registry, ChiCTR1900027399. Registered on 12 Nov 2019, http://www.chictr.org.cn/showproj.aspx?proj=43686.

## Background

Hemiplegia is one of the most common functional defects after stroke. Although stroke patients can recover spontaneously, most patients in the chronic phase will still suffer from upper limb dysfunction, especially hand dysfunction. It seriously affects the patients’ abilities of daily living, and imposes a heavy burden on their families and the society [1].

Transcranial magnetic stimulation (TMS), one of the non-invasive brain stimulation (NIBS) techniques, have been widely used in research and clinical treatment to promote the recovery of motor function in stroke patients due to its safety, noninvasiveness, and painlessness [2, 3]. Repeated TMS (rTMS) is a commonly used stimulation mode developed on the basis of TMS. High frequency rTMS (≥1 Hz) has an excitatory effect on cortex neurons, whereas low frequency rTMS (< 1 Hz) inhibits the activity of cortex neurons [4–6]. In recent years, rTMS has shown a great potential in stroke rehabilitation, with many studies reporting that it can improve the motor function of stroke patients with hemiplegia [7–10]. However, there are also studies reported contrasting results that rTMS does not confer additional benefits in the treatment of hemiplegia [11–14], with some studies even reporting mild functional regression after rTMS treatment [15, 16]. Moreover, recent reviews on the clinical efficacy of rTMS in the treatment of stroke hemiplegia did not reach a consistent conclusion, especially in patients with severe hemiplegia or at chronic stage [13, 17–20]. According to the Clinical Application Guidelines for rTMS (2018) [21], level A evidence supports the use of low-frequency rTMS on contralesional M1, and level B evidence suggests application of high-frequency rTMS on ipsilateral M1 in patients with sub-acute stroke. However, there is no clear recommendation for rTMS stimulation parameters in patients with chronic stroke. Therefore, this calls for high quality evidence that will be used to develop an optimal rTMS protocol for chronic stroke patients with severe hemiplegia.

The interhemispheric inhibition (IHI) model, which is commonly used as the fundamental theory for standardized rTMS treatment, was first proposed by Murase in 2004 [22], which suggests that the bilateral primary motor cortexes (M1) are connected through the corpus callosum in a balance of competing inhibition in healthy individuals. However, the IHI balance is disturbed after the onset of stroke, thereby leading to over activation of the contralesional hemisphere. Specifically, damage to the affect hemisphere weakens its inhibitory effect on the contralesional hemisphere, ultimately resulting in abnormally increased excitability of cM1. Notably, the over activation of cM1 will in turn inhibit the affect M1, causing a vicious circle. The disrupted balance between bilateral M1 will eventually hinder the motor output and impede the recovery of upper limb motor function in stroke survivors. Ideally, according to the standardized treatment protocol [19, 20], high-frequency rTMS is able to increase the excitability of affected M1, whereas low-frequency rTMS is capable of reducing the excitability of cM1, thereby enabling the disrupted IHI to reach a new equilibrium. However, some studies have found that the standardized rTMS protocol is not suitable for all stroke patients [11, 12]. It is worth noting that patients with severe hemiplegia seem to be less suitable for this standardized rTMS protocol [19]. This has led to some researchers questioning the value of classic IHI imbalance theory in clinical practice. Pino et al. [23] proposed the bimodal balance-recovery model in stroke recovery, which suggests that determining the mode of recovery to be adopted depends on the degree of damage to the affected hemisphere, namely structural reserve. For example, in patients with less damage (higher structural reserve), the classic IHI imbalance mode will dominate the recovery process, and the increased activation of contralesional hemisphere will not be conducive to motor recovery. In such cases, standardized low frequency rTMS of cM1 can exert therapeutic effects by inhibiting this abnormal excitability. In contrast, for patients with low structure reverse, the recovery process will be dominated by the compensatory mode because the increased motor cortex excitability on the unaffected side will be conducive to rehabilitation. In this case, the standardized low-frequency rTMS protocol might not be effective, and thus applying high-frequency rTMS on cM1 is a better option. Taking these two recovery models together, we believe that if we can identify the cut-off of structural reserve, we might be able to evaluate the real effects (inhibitory or compensatory) of the contralesional hemisphere on motor output. This will aid in selecting the optimum rTMS stimulation strategy on contralesional hemisphere (low frequency or high frequency).

In addition, studies should clarify whether the cM1 should be used as the only target brain area on the contralesional hemisphere in the compensatory model. According to the concept of “segregation” in classic brain research, different regions of the cerebral cortex have relatively different functions and each region is responsible for a specific functional task. In fact, even for the simplest functional tasks such as reaching, a wide range of different brain regions need to interact and coordinate to form a network to complete these tasks, a process referred to as “functional integration” [24]. Therefore, to complete a motor task, secondary motor areas like premotor cortex (PMC), supplementary motor area (SMA), cingulate motor area (CMA), and other moto-related brain regions may also be involved along with the primary motor cortex. However, most rTMS studies in stroke rehabilitation have only focused on M1. When the corticospinal tract (CST) is severely damaged, it is possible that the brain reorganization pattern may not only be associated with M1; the secondary motor cortex closely linked to M1 may also be involved [25].

Against this background and based on our previous studies [24–30], we propose that PMC might play a key role beyond M1. This can be attributed to several reasons. First, homologous regions of bilateral hemispheres are connected through the corpus callosum, and the connections between bilateral PMC form the largest proportion of white matter fibers of the corpus callosum, rather than between bilateral M1 [26]. This provides the structural basis for the existence of IHI in PMC as it is in M1. Thus, the interaction between bilateral PMC in stroke recovery is worth more attention. Second, PMC is composed of the dorsal part (PMd) and the ventral part (PMv). Previous studies revealed that PMd was involved in the coordination and control of the complex movements of hands [27]. Uncrossed corticospinal ventral tracts originating ipsilateral from PMd (approximately 10–20% of CST) were also found in animal studies [28]. Moreover, PMd is associated with the reticulospinal tract and the red nucleus spinal tract emanating from the brain stem, mainly inculcating the ipsilateral proximal limb [29]. This implies that cPMd may play a compensatory role in promoting motor functional recovery through the ipsilateral inculcating pathway. Third, we have previously conducted a resting-state fMRI study in chronic stroke patients, and found that the betweenness centrality (BC) of cPMd in the stroke group was significantly lower than that in the healthy group. In addition, the BC value of cPMd was significantly positively correlated with the score of the upper limb motor function on the ipsilateral side. These results suggest that the more compensatory effects cPMd provide, the better the motor prognosis for severe stroke patients [30]. Based on the above three points, we hypothesized that cPMd may play a role as a potential target brain area for promoting brain reorganization in rTMS therapy.

Currently, only sporadic reports of high frequency rTMS on cPMd in stroke treatment exist. Johansen-Berg et al. [31] stimulated the cPMd of stroke patients with mono-pulse TMS, and found a negative correlation between the stimulus intensity and the lateral index of PMd activation in task-based fMRI, as well as a positive correlation to the hemiplegic hand motor function score. This suggests that TMS is capable of activating excitatory effects on cPMd, and facilitating the motor recovery of upper limb and hand in stroke patients. In addition, Bestmann et al. [32] found that stroke patients with more severe dysfunction demonstrated more activation in cPMd and the posterior part of M1 (BA4p) on the affected side when a single high-frequency TMS stimulated cPMd. This suggests that exciting cPMd with single high-frequency TMS may cause the activation points of the affected hand projection cortex to shift backward, thereby promoting functional recovery. A recent randomized sham-controlled crossover study published in 2017 compared the effects of single-pulse low-frequency TMS on M1, high-frequency TMS on cPMd, and sham stimulation in 15 stroke patients. The results showed that treatment using single-pulse high-frequency TMS on cPMd resulted in a greater improvement than using single-pulse low-frequency TMS on cM1 in severely affected patients [33]. However, these evidences were all based on cross-sectional studies, and longitudinal treatment studies on single-pulse high-frequency rTMS of cPMd are still lacking. Moreover, most of the existing studies utilized single-mode fMRI analysis, which could not thoroughly demonstrate the brain network reorganization patterns of rTMS in promoting functional recovery in stroke patients. Therefore, future studies should use multimodal fMRI (structural, functional, and effective network) to elucidate the mechanisms of this new protocol of rTMS in stroke rehabilitation from multiple perspectives of neural repair and remodeling.

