### Aims and hypotheses

This study will conduct a longitudinal, single-blinded, randomized controlled trial to verify the clinical effects of different protocols of rTMS therapy on functional recovery of chronic subcortical stroke patients with severe hemiplegic upper limb. To the best of our knowledge, this is the first study to compare the effects of low-frequency rTMS on cM1 and high-frequency rTMS on cPMd. We expect that the findings will provide vital information about the optimal rTMS strategy. Multimodal fMRI scanning and electrophysiological measurements will be performed longitudinally to elucidate the underlying neural mechanism of brain reorganization after different parameters of rTMS therapy. We hypothesize that high-frequency rTMS on cPMd might be the optimal protocol for motor functional recovery in chronic subcortical stroke patients with severe hemiplegia. This clinical effect may be attributed to the specific remodeling patterns of structural, functional, or effective connectivity of homologous or allogeneic cortexes within or between hemispheres through multimodal neural imaging analysis. Furthermore, joint analysis of the clinical and neuroimaging results might identify the cut-off of structural reserve that determines the application of high/low frequency rTMS on contralesional hemisphere to achieve maximum functional recovery of the paretic upper limb.

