#### DTI

The bilateral posterior limb of internal capsule (PLIC), bilateral cerebral peduncle, and corpus callosum of each patient will be delineated manually by two radiologists. For each patient, the common part of the results recorded by the two radiologists will be adopted as the regions of interest (ROIs). The mean fractional anisotropy (FA) will be calculated with all the ROIs for each hemisphere. Notably, FA asymmetery index (FA AI) is defined by the following formula:

$$FA\ AI=\frac{\left({FA}_c-{FA}_a\right)}{\left({FA}_c+{FA}_a\right)}$$where FAc is the FA of the contralesional hemisphere and FAa is the FA of the affected hemisphere. FA AI can be used to quantitatively evaluate the structural integrity of CST and corpus callosum.

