#### Group-level analysis

All statistical analyses will be performed using SPSS software (SPSS 25.0, SPSS Inc., Chicago, Illinois). The intention-to-treat principle will be used for the analysis of functional and electrophysiological data. One-way analysis of variance (ANOVA) will be used to compare the demographic characteristics and baseline assessment (T0) of all outcomes among groups. To compare the treatment effects of different rTMS protocol, a two-way mixed design ANOVA with between-subject factor “Group” and within-subject factor “Time” will be performed for the clinical and electrophysiological changes. Moreover, Bonferroni correction will be employed for post hoc multiple comparisons. *P* < 0.05 will be considered statistically significant for all analyses.

For rs-fMRI and DTI data, a two-way mixed design ANOVA will be performed, with between-subject factor “Group” and within-subject factor “Time” on the data generated in the data processing step, including Eg, El, network betweenness, clustering coefficient, and FA AI. For tb-fMRI data, a whole brain paired T-test will be performed between the task state blocks and baseline blocks in the FC group, and the voxels whose t value is higher than the threshold will be regarded as the activated brain region. For cM1-LF, cPMd-HF, and CON groups, a two-way mixed design ANOVA, with between-subject factor “Group” and within-subject factor “Time” will be performed within the former activated brain region. The most significant point of “Group” × “Time” effect in the activated brain region will be used as the center to construct spherical balls with a radius of 6 mm, and the spherical balls will be regarded as the ROIs. Finally, to obtain the effective connectivity of each patient at different time points, the average time series of all voxels in each ROI will be subjected to dynamic causal model (DCM) analysis.

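### The single DTI test variable, FA AI, mixes a midline structure into a left-right index and so cannot test the between-hemisphere structural-connectivity part of the hypothesis

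*Protocol article*

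**What the plan says.** **Rationale and hypothesis.** The Background gives three reasons for targeting cPMd. The first is that "the connections between bilateral PMC form the largest proportion of white matter fibers of the corpus callosum, rather than between bilateral M1". It also states that "future studies should use multimodal fMRI (structural, functional, and effective network") to explain the mechanism. Aims and hypotheses then says that the clinical effect may be due to "specific remodeling patterns of structural, functional, or effective connectivity of homologous or allogeneic cortexes within or between hemispheres".

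**DTI regions and metric.** The DTI section states: "The bilateral posterior limb of internal capsule (PLIC), bilateral cerebral peduncle, and corpus callosum of each patient will be delineated manually by two radiologists". It continues: "The mean fractional anisotropy (FA) will be calculated with all the ROIs for each hemisphere". The index is FA AI = (FAc − FAa)/(FAc + FAa), with c the contralesional and a the affected hemisphere. The section adds that "FA AI can be used to quantitatively evaluate the structural integrity of CST and corpus callosum".

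**Test.** Group-level analysis enters the rs-fMRI and DTI data in a Group by Time mixed ANOVA, "including Eg, El, network betweenness, clustering coefficient, and FA AI". The first four are the rs-fMRI graph measures, so FA AI is the only DTI variable named. Functional connectivity has a 90-node matrix (Rs-fMRI section), and effective connectivity has DCM on the task data (Group-level analysis).

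**The concern.** The structural argument for cPMd concerns fibres that cross between the hemispheres, and it distinguishes premotor from M1 fibres. The planned DTI variable is a left-right asymmetry index. The PLIC and peduncle are paired and carry descending fibres, so an asymmetry index suits them. The callosum joins the two sides. A change in it tends to enter both hemisphere means, and an asymmetry index largely cancels such a change.

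At stake is the interpretation of the DTI result. A null FA AI result would say little about callosal remodelling. A positive one could reflect the CST, the callosum or both, and could not be assigned to premotor or M1 fibres. DTI is the trial's only structural-connectivity measure, so no other planned analysis fills the gap.

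**Working it through.** The plan states no FA figures, so there is none to reproduce. The check asks how far FA AI, as defined, responds to a callosal change.

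**Assumed inputs (not in the document).** PLIC FA 0.65 contralesional and 0.50 affected; peduncle 0.65 and 0.52; callosum 0.60, taken as one midline value that counts for both hemispheres. The three regions are weighted equally.

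**Step 1: callosum alone.** If the index is formed region by region, then FAc = FAa for the callosum, and FA AI = 0 at any callosal FA. It carries no information.

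**Step 2: callosum pooled into the hemisphere mean, as the DTI section reads.** The divisor 3 cancels, so sums can be used.
- Contralesional sum: 0.65 + 0.65 + 0.60 = 1.90. Affected sum: 0.50 + 0.52 + 0.60 = 1.62.
- FA AI = (1.90 − 1.62)/(1.90 + 1.62) = 0.28/3.52 = 0.0795.
- Callosal FA 0.65: 0.28/3.62 = 0.0773.
- Callosal FA 0.70: 0.28/3.72 = 0.0753.

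A callosal rise of 0.10 lowers the index by 1 − 3.52/3.72 = 5.4% of its value. A callosal gain thus appears as a slight fall in asymmetry.

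**Step 3: the same shift from the CST.** Hold the callosum at 0.60 and raise affected PLIC FA by x: FA AI = (0.28 − x)/(3.52 + x). With x = 0.014 this is 0.266/3.534 = 0.0753. A rise of 0.014 in one descending-tract region gives the same index value as a rise of 0.10 in the whole callosum, about one seventh of the size. The index cannot tell the two apart.

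**Step 4: sensitivity to the assumptions.** With S the sum over both hemispheres, a rise δ common to both sides changes the index by the factor S/(S + 2δ). The relative change does not depend on the assumed asymmetry. For a mean regional FA of 0.5 to 0.7, S runs from 3.0 to 4.2, and δ = 0.10 gives a fall of 0.2/3.2 = 6.3% to 0.2/4.4 = 4.5%. If the callosum had weight 2/3 (for example by volume), the hemisphere means would be 0.6167 and 0.5700. The index would be 0.0467/1.1867 = 0.0393, falling to 0.0467/1.3200 = 0.0354, or 10%. More callosal weight makes the index somewhat more responsive but halves its starting value.

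**Step 5: effect on the reserve marker.** Without the callosum, FA AI = (1.30 − 1.02)/(1.30 + 1.02) = 0.28/2.32 = 0.1207. Including it dilutes the CST asymmetry to 0.0795, 34% lower.

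**Step 6: premotor versus M1.** Whatever the FA values, one mean per hemisphere over all regions has no term specific to premotor or to M1 crossing fibres.

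**The case against.** The case against has several parts.

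- **It is a condensed article.** Callosal subdivision and tractography are details that a full protocol or SAP may hold, and the list of test variables is introduced by a word that leaves it open. This stands as far as subdivision goes: the article does not say that the callosum is one region. But the regions, the pooling, the formula and the test variable are stated, and no other DTI variable is defined. The gap lies in a stated choice.
- **The Background only justifies a target.** This stands. A reason for choosing cPMd need not become an endpoint. The test that matters is against Aims and hypotheses, where structural connectivity is named.
- **The hypothesis is hedged and disjunctive.** This stands. Functional and effective connectivity each have an analysis between areas, so only the structural part is affected.
- **DTI has a narrower role.** The Discussion gives it the remodelling of the motor pathway, and PLIC and peduncle serve that and the structural-reserve aim. This is fair, but the DTI section also claims that FA AI evaluates the callosum, which the index does poorly.

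A reader might go further and infer that the DTI plan measures no link between cortical areas at all. The documents do not support this. The callosum is drawn, and the Background says that homologous regions connect through it, so callosal FA analysed in its own right would be a coarse between-hemisphere measure. The fault is that it is folded into FA AI.

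**Conclusion.** The concern holds in a limited form. FA AI as defined is mainly an index of descending-tract asymmetry. It barely registers a midline callosal change (about 5% of its value for a rise of 0.10, with a range of 4.5% to 10% under the assumptions tried), and it cannot assign a change to premotor or M1 fibres. It therefore cannot test the between-hemisphere structural-connectivity part of the hypothesis, and it does not fully support the statement that it evaluates callosal integrity.

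The percentages rest on assumed FA values and on one callosal value counted for both sides. If the callosum were split at the midline, a change common to both halves would still mostly cancel, and a one-sided change would be read as asymmetry. The lack of premotor or M1 specificity needs no assumption.

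A reader might also infer a definite loss of power for a premotor effect. The documents cannot support such a figure: they give neither the premotor share of the callosum nor an effect size, and whole-callosum FA is not a named test variable.

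The point affects a secondary, mechanistic aim. The clinical comparison is untouched.

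**What to change.** 1. Compute FA AI from PLIC and peduncle only, and keep it as the marker of CST structural reserve.
2. Enter callosal FA as a separate variable in the Group by Time model, with the region already to be drawn split into premotor and motor segments. State the multiplicity control for these added outcomes.
3. Treat tractography of the PMd-PMd, M1-M1 and PMd-M1 connections as optional and exploratory. It is the only step that would reach links within a hemisphere, and tract FA is less reliable near lesions.
4. If steps 2 and 3 are not wanted, narrow the structural claim in Aims and hypotheses to CST integrity, and amend the DTI section's statement about the callosum.

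The 64-direction DTI data are already planned for patients at T0, T1 and T2, so no extra scan or patient is needed. The cost is analysis time and a few more, noisier imaging outcomes. Step 4 costs only a change of wording.
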